#### Chinese Herbal Medicines

The Chinese herbal formula of Modified Bai He Gu Jin Tang (including Rehmanniae Radix 10 g, Rehmanniae Redix Praeparata 10 g, Ophiopogonis Radix 10 g, Lilii Bulbus 15 g, Paeoniae Radix Alba 10 g, Angelicae Sinensis Radix 10 g, Fritillariae Thunbergii Bulbus 5 g, Glycyrrhizae Radix et Rhizoma 10 g, Platycodonis Radix 15 g, and Salviae Miltiorrhizae Radix et Rhizoma 15 g) will be prescribed in granules. The rationale for the formula selection is as follows: (1) based on the syndrome differentiation, pulmonary fibrosis post–COVID-19 appears as qi-yin deficiency of the lung [32]; (2) a previous study has shown that many herbs using this formula and Salviae Miltiorrhizae Radix et Rhizoma have antifibrosis effects [33]; and (3) Bai He Gu Jin Tang has the effects of nourishing lung qi and ying deficiency [34]. Therefore, the formulation of Bai He Gu Jin Tang was modified to match the therapeutic purpose. A dose of 10 g per day (5 g, twice per day) will be ingested. Patients will dissolve a sachet of granules (5.0 g) in 200 ml of hot water twice per day after breakfast and dinner, 7 days per week, for 3 months. The entire manufacturing process will be in strict compliance with the standards of good manufacturing practice.

#### Waiting List Control

The waiting list control sign will be adopted to conceal the allocation results from the patients as well as to reduce selection and confounding bias and increase the participants’ adherence to the study. Patients in the waiting list control group will receive no treatment in the study period (including a 12-week intervention period and a 12-week follow-up period). However, they will receive Chinese herbal medicines after the completion of the study (ie, after the third wave of measurements in the 25th week).

### Outcomes

Table 2 lists a description of the outcomes and other measures, which are not exhaustive. All measurements will be recorded at baseline and repeated at the 13th and 25th weeks of the study. Patients will be assessed for risk prior to data collection. Further information from patients using appropriate data collection methodologies, including clinical symptoms, treatment history, comorbidities, physical activity, nutrition, and other potential variables, will be obtained and adjusted for during data analysis.

**Table 2 table2:** Description of the outcome measures.

Measure		Outcomes
Cardiorespiratory fitness		Six-minute walk test Performance time test
Dyspnea		Borg Category-Ratio 0-10 Scale (Borg Dyspnea Scale)
Body composition		BMI Waist circumference Stature Body mass Segmental muscle mass Anatomical circumference
Lung function test		Forced vital capacity Forced expiratory volume 1 Forced expiratory volume 1/forced vital capacity Fractional exhaled nitric oxide DLCO^a^
Cardiopulmonary exercise test/blood gas		VE^b^ VCO_2_^c^ VO_2_^d^/PCO_2_^e^ PO_2_^f^
**Blood biochemistry tests**		
	Metabolic function	Insulin
	Immune function	Coagulation Lymphocytes CD3 CD4 CD8 CD19 CD16+CD56 T cells
	Neurological function	BDNF^g^ Corticosterone
	Cytokine profiles	Interleukin 1 Interleukin 6 Tumor necrosis factor alpha
Gut microbiome		Fecal metagenomics analysis
Glucose, fructose, and related metabolites		UPLC-QTOF-MS^h^ analysis
Metabolomics-related measurement of depression		Metabolomics analysis of selected neurotransmitters as potential markers of depression
Quality of life and other mental health–related measures		Self-reported scales

^a^DLCO: diffusing capacity of the lungs for carbon monoxide.

^b^VE: ventilation.

^c^VCO_2_: carbon dioxide output.

^d^VO_2_: oxygen uptake.

^e^PCO_2_: partial pressure of carbon dioxide.

^f^PO_2_: partial pressure of oxygen.

^g^BDNF: brain-derived neurotrophic factor.

^h^UPLC-QTOF-MS: ultra-performance liquid chromatography coupled with quadrupole/time-of-flight mass spectrometry,

### Outcome Measures

#### Cardiorespiratory Fitness

Functional exercise capacity that reflects daily physical activities will be assessed using the six-minute walk test (6MWT) to assess the outcome of the intervention. This test is recommended by the American Thoracic Society to evaluate the global and integrated responses of all the systems involved during exercise, including the cardiopulmonary systems, systemic and peripheral circulation, blood, neuromuscular units, and muscle metabolism. Heart rate and blood pressure will be measured before and after exercise. The test has high test-retest reliability (intraclass correlation coefficient=0.88-0.91) [35].

#### Dyspnea

Dyspnea is a common exercise-induced symptom of disease and usually occurs in patients with pathophysiology that results in inefficient gas exchange and ventilator impairments. The Borg CR10 Scale (Borg Dyspnea Scale) will be used to rate the dyspnea and overall fatigue levels of the patients at the beginning and end of the 6MWT. The scale will also be used during the cardiopulmonary exercise test (CPET).

#### Body Composition

Segmental muscle mass and BMI (kg/m^2^) will be used to assess the body composition of the patients. A bioimpedance analysis approach (InBody 770 analyzer, InBody Co, Ltd) will be used to assess the patients’ segmental muscle mass. A stadiometer (Seca 284, Seca Corporation) will be used to measure stature and body mass. Anatomical circumference will be measured using a distensible measuring tape.

#### Lung Function

The FVC test, forced expiratory volume (FEV_1_), and FEV_1_/FVC ratio will be assessed to indicate the functional severity and capacity of the patients’ lungs (Vmax Encore V229, VIASYS Respiratory Care Inc). Fractional exhaled nitric oxide (FeNO) will be used to assess inflammatory response to exercise and medicinal intervention (NObreath, Bedfont Scientific Ltd, England).

#### Cardiopulmonary Exercise

The CPET will be performed using the Vmax Encore V229. The CPET provides information concerning the level of exercise that the patient can perform without undue stress. The test results will guide the research team regarding the prescription of exercise for physical rehabilitation methodologies. It also provides quantitative evidence of the benefits of a rehabilitation program as well as information on the mechanisms involved. Improvement in exercise tolerance cannot be objectively assessed without CPET [36]. An incremental ergometry exercise test (Excalibur ergometer, Lode Ergometry), will be used to assess the responses of the cellular, cardiovascular, and ventilatory systems under precise conditions of metabolic stress. Breath by breath measurements of minute ventilation (VE), carbon dioxide output (VCO_2_), O_2_ uptake (VO_2_), VE/VCO_2_, VE/VO_2_, deviation in the responses from the pulmonary to cellular respiration and arterial blood gas, partial pressure of carbon dioxide (PCO_2_), and oxygen saturation as measured by pulse oximetry (SpO_2_, Sentec AG), will be monitored continuously during the exercise test. Depending on the physical condition of the patients, modification of the protocols to smaller work rate increments may be warranted. Intensities and durations will be specific to each individual to facilitate measurement and data capture. Before each test, the O_2_ and CO_2_ analyzers of the CPET system will be calibrated using standard gases (Gas 1: O_2_: 25.89%, CO_2_: 0%; Gas 2: O_2_: 16.44% CO_2_: 3.89%), and the flow volume integration system will be was calibrated by applying a standard volume (3 L) of gas at various flow rates. Canopy studies within the Vmax software suite will be used to validate the accuracy of the gas-exchange measurement instruments that measure VO_2_ and VCO_2_ using the methanol burning technique. The ratio of VCO_2_ to VO_2_ in the combustion of methanol yields a respiratory quotient (RQ) of 0.667. We will use a 3% difference as the accuracy threshold for measured RQ (RQ range of 0.647-0.687).

#### Quality Assurance, Calibration, Accuracy, and Precision for the Laboratory-Based Assessment Measures

All the devices used for measurement will be calibrated according to the manufacturer's specifications. The protocols of the measurements and sources of variability will be controlled by following the standards outlined in the American Thoracic Society calibration guidelines for spirometers and gasometers. Anatomical circumference measurements will be adopted from the anthropometry procedures manual provided by the US Centers for Disease Control and Prevention [37]. Repeated tests will be performed at the same time of day in a controlled laboratory environment of constant humidity, temperature, and pressure. Patients will arrive at the laboratory at designated times for all physiological and clinical assessments. All patients will be transported to the laboratory for testing and returned home by coach. A recovery period will be observed postassessment to ensure that the participants have no negative responses to the measurements. Once the recovery period is complete, all participants will be returned home.

#### Blood Biochemistry

Venous blood will be drawn at 3 time points, namely at pretreatment, at posttreatment, and after the 12-week follow-up. After coagulation at room temperature for 30 minutes, the samples will be centrifuged at 3000 rpm for 20 minutes. Serum as the supernatant will be extracted and stored at –80 ˚C until assay. Serum levels of insulin will be assessed by a commercially available enzyme-linked immunosorbent assay (ELISA) kit (Merck & Co). Serum will be isolated by centrifugation (1000 rpm for 30 minutes, 4 °C) and stored at –80 °C until analysis. The prothrombin time test will be used to measure blood coagulation. Venous blood will be collected by venepuncture in a tube with sodium citrate. Plasma will be isolated after centrifugation at 1000 rpm for 30 minutes at 4 °C. Thromboplastin will be added to the plasma and maintained at 37 °C for 2 minutes. Calcium chloride will be added to the mixture, and the plasma will be allowed to coagulate. The time needed for the coagulation will be recorded as the prothrombin time.

Flow cytometry for counts of main lymphocyte subpopulations (CD3, CD4, CD8, CD19, and CD16+CD56 T cells) will be performed to test immune function. Venous blood will be stored in tubes with EDTA (anticoagulant). 100 µL of blood will be stained within 24 hours of sampling by the BD Multitest 6-color TBNK reagent (BD Biosciences). The lymphocytes with the antigens CD3, CD4, CD8, CD19, and CD16+CD56, which are the main populations of lymphocytes, will be labelled by a fluorochrome-conjugated antibody in the reagent. The whole blood will be incubated in the reagent at room temperature for 30 minutes, and red blood cells will be lysed with ammonium chloride solution. Cell sorting and analysis will be performed with a BD Accuri C6 flow cytometer (BD Biosciences). Each subpopulation of lymphocytes will be expressed in absolute value and percentage of total lymphocytes.

As suggested by Hacimusalar and Eşel [38], the following markers related to emotional disturbances will be studied.

##### Brain-Derived Neurotrophic Factor

Serum concentration of brain-derived neurotrophic factor (BDNF) will be measured with a commercially available ELISA kit (Millipore) according to the manufacturer’s instructions.

##### Corticosterone

Serum concentration of corticosterone will be assayed by ELISA kit (Enzo Life Sciences, Inc) according to the manufacturer’s instructions.

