## Methods

### Study Design

The proposed study will be a triple-blinded randomized controlled trial comprising four groups: (1) a cardiorespiratory exercise plus Chinese herbal medicines group, (2) a cardiorespiratory exercise group, (3) a Chinese herbal medicines group, and (4) a waiting list group. The target population will be postdischarge adult patients recovering from COVID-19 who were diagnosed with pulmonary impairments. Recruitment will take place in Hong Kong via our International Rehabilitation Network Center for Patients With COVID-19. The proposed rehabilitation period will last for 12 weeks, with a 12-week follow-up [14]. Primary outcomes will include the clinical symptoms of pulmonary fibrosis (dyspnea, fatigue, lung function, blood oxygen levels, immune function, blood coagulation, and related blood biochemistry). Blood biochemistry will be further analyzed using unique metabolomics techniques to identify potential synergies related to immune function response to the interventions [15]. We will investigate glucose metabolism and its association with the degree of infection and prognosis. We will also profile the gut microbial metabolome to establish associations between (virus-induced) dysbiosis and the outcomes of COVID-19 infection. Pulmonary function tests will be completed using clinical spirometry, as outlined by the American Thoracic Society. Blood gas levels, immune function, and coagulation levels of the patients will be measured pre- and post-intervention in venous blood samples [16]. The trial has been registered on ClinicalTrials.gov (NCT04572360). A flow diagram of the trial is shown in Figure 1.

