### Eligibility Criteria

The target population will be adult patients with COVID-19 who have been discharged from the hospital and are still experiencing respiratory impairments. Patients will be recruited from Hong Kong. Inclusion criteria will include (1) age ≥18 years; (2) discharged from hospital for no less than 4 weeks; (3) percentage of predicted forced vital capacity (FVC) <90% or a percentage of predicted carbon monoxide diffusing capacity <90% [17]; (4) smartphone user; (5) able to communicate in Cantonese or Mandarin. Exclusion criteria will include (1) being pregnant or planning to become pregnant in the coming 6 months; (2) having acute exacerbations in the 12 weeks preceding recruitment; (3) having any contraindications for exercise (eg, physical disability, uncontrolled mental disorders, unstable heart disease, inability to perform muscle strength tests) [18]. The last two exclusion criteria will be evaluated by a physician.

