#### QoL and Other Mental Health-Related Measures (Self-Reported)

QoL will be measured using the Personal Well-being Index-Chinese Version. It is a subjective QoL measure that has been translated and validated. Anxiety will be measured using the Chinese version of the Depression Anxiety Stress Scale-21, which has been proven to have internal consistency [44,45]. The scale will discriminate between the negative emotional syndromes of depression, anxiety, and stress in Chinese populations. Only the subscales of anxiety and stress will be used. Loneliness will be measured using the Revised UCLA Loneliness Scale) [46,47]. This scale consists of 20 items and has been widely used to assess loneliness in research. General mental health will be measured using the General Health Questionnaire, which is commonly used to screen minor psychiatric symptoms [48].

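### The plan measures serum corticosterone, a minor glucocorticoid in humans, as a marker of emotional disturbance in adult patients, and neither measures cortisol nor says why

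*Protocol article*

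**What the plan says.** The analyte appears in two places, and they agree. Table 2, under blood biochemistry tests, has a row for neurological function that reads "BDNF^g^ Corticosterone". The Corticosterone subsection fixes the matrix, the method and the kit maker: "Serum concentration of corticosterone will be assayed by ELISA kit (Enzo Life Sciences, Inc) according to the manufacturer’s instructions".

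The purpose is given in the Blood Biochemistry section, which says, with a citation, that "the following markers related to emotional disturbances will be studied". Subsections on BDNF, corticosterone and cytokines follow.

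The Eligibility Criteria settle the species: "The target population will be adult patients with COVID-19 who have been discharged from the hospital".

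Blood Biochemistry also says that venous blood is drawn before treatment, after treatment and after the 12-week follow-up, and that serum is frozen at –80 °C until assay. The section on quality assurance for laboratory-based measures has repeated tests done at the same time of day.

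Cortisol is not mentioned anywhere in the article.

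**The concern.** Corticosterone is the main glucocorticoid of rodents. In humans that place belongs to cortisol, and corticosterone is a minor hormone beside it. A human trial that wants a blood glucocorticoid as a marker of emotional disturbance would be expected to measure cortisol. Naming only corticosterone, without explanation, may be a slip for cortisol or a carry-over from animal work. The article does not show which.

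What is at stake is how the result can be read. The mixed model will compare groups on the outcome variables. If the groups do not differ on corticosterone, little follows about the main human glucocorticoid. If they do differ, the meaning is uncertain, because the planned analyte is the minor hormone and its companion was not measured.

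**Working it through.** The article gives no figure to reproduce, because the point concerns the choice of analyte. The check sets the relevant places side by side.

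1. **Is the analyte fixed?** Yes. Table 2 and the Corticosterone subsection name the same hormone, and the latter names serum, ELISA and the manufacturer. This is not detail left to a fuller document. There is no internal contradiction, and a text-extraction fault is unlikely because the word stands in both places.

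2. **Is the population human?** Yes: discharged adult patients.

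3. **What is the marker for?** Blood Biochemistry says emotional disturbances, and Table 2 files it under neurological function. The article goes no further.

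4. **Is there a stated reason, or a companion cortisol measurement?** Neither. The only support is the citation that introduces the whole group of markers. That source is not at hand, so whether it supports corticosterone in humans is unknown.

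5. **What depends on the analyte?**
   - Sample size: 172 patients (43 per group) rest on an effect size of 0.8 from a meta-analysis of exercise effects on dyspnea and exercise capacity. Corticosterone plays no part.
   - Mediation: Statistical Analysis plans it for the gut microbiome and the immune function tests. Table 2 lists corticosterone under neurological function, not immune function.
   - Mental health objective: anxiety, stress, loneliness and general mental health have self-report scales. For the Depression Anxiety Stress Scale the article says: "Only the subscales of anxiety and stress will be used". Stress is therefore scored whatever the assay shows.

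6. **How many assays are involved?** At most 172 patients × 3 draws = 516 samples.

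7. **Can cross-reaction be sized?** Not from the article. Suppose cortisol stands at r times corticosterone and the antibody picks up a fraction x of it. The false share of the reading is then r·x / (1 + r·x). The values of r and x below are assumptions, not figures from the article:
   - r = 10, x = 0.05%: 0.005 / 1.005 = 0.5%
   - r = 50, x = 0.3%: 0.15 / 1.15 = 13%
   - r = 50, x = 2%: 1 / 2 = 50%

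   The result runs from negligible to severe. It shows why the kit's cross-reactivity should be known, and does not show that a problem exists.

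**The case against.** The strongest reply is that the article promises little for this marker. It never calls corticosterone a stress hormone, never says that it marks the human stress response, and never makes it the link between the interventions and mood. A reader might infer that the trial's stress measurement fails. The text does not support that: the stated purpose is only a relation to emotional disturbances, and stress has its own self-report subscale. BDNF, the cytokines and the neurotransmitter metabolomics are further related markers, so losing this analyte would leave every stated aim testable. All of this stands, and it limits the consequence.

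A second reply is that corticosterone does circulate in humans, so the assay is not empty. This also stands. Weak or indirect is the fair description; uninformative would be too strong.

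A third reply is that the cited source may justify the choice. It may, but the article gives no reason of its own, and a citation for a group of markers does not explain why the minor hormone is measured without the main one.

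A reader might also infer that a primary outcome is compromised, because the Study Design section counts "blood oxygen levels, immune function, blood coagulation, and related blood biochemistry" among the primary outcomes and Table 2 puts corticosterone under blood biochemistry tests. The article does not name corticosterone as primary, and its first objective ties the primary outcome to pulmonary function. The loose wording leaves the analyte's tier unclear, but that is not enough to call it a primary endpoint.

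**Conclusion.** The point holds in a limited form. The plan fixes a minor human glucocorticoid as a marker of emotional disturbance in adults, omits the main one and gives no reason. Followed as written, it yields a weaker marker than the same serum could provide. This rests on one premise from outside the article, which is general physiology and not any single source: cortisol is the principal glucocorticoid in humans and corticosterone a minor one.

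The size is one biomarker at three time points. No sample-size figure, error rate or planned mediation model changes. Treating it as exploratory is an inference from the objectives and the analysis section, not a label the article uses. Cortisol cross-reaction remains an open question of unknown size. The change is worth making because it is simple, not because the trial's conclusions hang on it.

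**What to change.** Change the analyte to serum cortisol in Table 2 and in the Corticosterone subsection, measured in the serum stored at the three time points. State explicitly that blood draws follow the same-time-of-day rule in the quality assurance section, which does not name them.

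If corticosterone is truly intended, say why it is informative in humans, report the kit's cross-reactivity with cortisol, and measure cortisol alongside it in the same samples.

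The cost is a different kit, or one added assay on at most 516 existing samples, and a short amendment. No extra visit or blood draw is needed, provided that enough stored serum remains. The article gives no assay prices, so the two kits cannot be assumed to cost the same.

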##### Cytokine Profile

The serum concentrations of interleukin-1, interleukin-6, and tumor necrosis factor alpha will be assayed by multiplex cytokine analysis. A multiplex cytokine kit (20-plex, Bio-Rad Laboratories) will be used according to the manufacturer’s instructions. The result will be generated by the Bio-Plex 200 suspension array system (Bio-Rad Laboratories) that is available in the University Life Science facility of Hong Kong Polytechnic University.

#### Gut Microbiome Test

All patients will be requested to self-sample their first morning feces by following detailed printed instructions. Collected stool samples will be immediately frozen in a home freezer (–20 ℃), then transported to our facilities in a provided freezer pack and stored at –80 ℃ for long-term use. Total DNA of 200 mg fecal samples will be extracted and purified as described [39]. The DNA concentrations and size distributions will be estimated using a NanoDrop instrument (Thermo Scientific) and agarose gel electrophoresis, respectively. The DNA one-paired-end library will be prepared using a TruSeq DNA HT Sample Prep Kit (Illumina Inc), and whole-genome shotgun sequencing of the samples will be carried out using the HiSeq 2000 platform (Illumina Inc). Low-quality reads with N bases, adapter contamination, or human DNA contamination will be filtered from the raw data, and the remaining high-quality sequences will be mapped with the published gene catalog of reference genes in the human gut microbiome [40]. Taxonomic assignment of the predicted genes and

Kyoto Encyclopedia of Genes and Genomes (KEGG) analysis will be performed as described previously [41]. The relative abundances of phyla, genera, species, and KEGG orthologs will be calculated from the relative abundances of the respective genes. For data analysis, the quantitatively measured metabolites for each participant will be merged into the participants’ clinical information through their individual sample IDs.

